**Fig. 2 Fig2:**
[figure not shown]
Sequential, multiple assignment randomized trial (SMART) design

### Setting

This study will be conducted in partnership with the second largest FQHC serving low-income and uninsured San Diegans and has a long-standing relationship with UC San Diego. This study will focus on clinics in Central, North, and East San Diego that serve refugee, immigrant, BIPOC, and Latino populations. San Diego has historically been one of the California counties with the highest number of immigrant and refugee families [65]. This FQHC has been successful in the early phases of COVID-19 vaccine campaigns in many regions but anticipates challenges with sustaining the level of support needed to keep up with guidelines as policy changes supporting COVID-19 vaccine efforts may wane in coming months and years. As shown in Table 1, the three target clinics serve a racially/ethnically diverse patient population whose primary preferred languages are Vietnamese (clinic 1), Arabic (clinic 2), and Spanish (clinic 3). Engagement in preventive services as shown by recommending screenings is lower than recommended in all clinics. In addition, the FQHC has a robust care coordination program in place as part of their PCMH accreditation. Taken together, these factors well position the partnering FQHC to collaboratively deliver a multi-level community-focused intervention to support equitable vaccine uptake and preventive services engagement.

**Table 1 Tab1:** Patient characteristics by participating Federally Qualified Health Center clinics

	Clinic 1	Clinic 2	Clinic 3
**Patient volume**			
Total no. of patients/site	2573	1751	1528
**Race/ethnicity**			
Asian	44%	68%	5%
Black	9%	2%	5%
White	26%	24%	55%
Latino	22%	7%	44%
**Preferred language**			
Arabic	0.1%	68%	0.4%
Spanish	7%	3%	18%
Vietnamese	32%	No data	0%
**Preventive health services**			
Blood pressure (any time)	74%	93%	89%
HbA1c screening (any time)	57%	56%	71%
**Community-level data by zip code**^**a**^			
COVID-19 positivity (rate per 100,000)	22,589	24,530	23,427
COVID-19 vaccination (rate per 1000)	807	745	803

^a^Source: County of San Diego Health and Human Services Administration from 2022

### Participants

A total of 300 adult patients (100 per clinic), from a sampling frame of approximately 5000 patients, will be recruited to participate in the study. Patient recruitment will occur at each of the three participating FQHC clinics through collaborative efforts between the FQHC’s care coordinators and the Community Weavers. The CABs will be invited to co-develop culturally appropriate recruitment methods to ensure participation from Spanish, Arabic, and Vietnamese-speaking patients connected with the partnering FQHCs. A weighted sampling approach will be considered if patient volume varies considerably between the three clinics during the baseline period. Furthermore, to understand reach of the program, characteristics of those participating in the study will be compared to the population in each of the three geographic regions recruited into the study.

### Procedures

#### Community engagement through CABs and Community Weavers

The multicomponent strategy will be developed and optimized using the team’s established co-creation approach with guidance from the Community Weavers and engagement of the community through CABs. Community Weavers will be hired and supervised by the study’s community partner, the Global ARC, based on their established relationships with ethnically based community organizations. Hiring criteria for Community Weavers include that they are fluent in English and at least one of the three priority languages (Spanish, Arabic, Vietnamese); are engaged with communities living near one of the three partnering FQHC clinics; have experience with community engagement, leading and organizing; and have the capacity to share back knowledge and information with their community as well as share the community’s perspectives and concerns with the CABs.

Community Weavers will have a critical role in developing and refining tailored mHealth messages [66]. They will also be instrumental in facilitating the existing care coordination efforts at the FQHC by focusing on immigrant and refugee communities that can be difficult to engage in care. The Community Weavers will lead three CABs that include five members each inclusive of the three primary languages spoken by community members of our clinics of interest. CAB members will be compensated for their time. In addition to the five community members, we will include the two care coordinators, a mHealth Specialist, and two clinical investigators as nonvoting members in each CAB.

During the first year, each CAB will meet up to four times. These initial meetings will be tasked with co-creating culturally and linguistically appropriate content and frequency for mHealth outreach and identifying topics, strategies, and processes for the care coordination program. mHealth outreach messages will be developed in the native languages of the CABs, and we will use professional translation as needed. To facilitate mHealth message development, Community Weavers will use a storytelling/narrative framework approach inviting residents to join open dialogue and share their journey through the decision-making process towards getting vaccinated, reflecting on the anxieties they navigated, the misinformation they were confronted with, and any structural or technological barriers they had to overcome to enhance the cultural resonance and tailoring of the mHealth messages [67]. In subsequent years, the CABs will continue meeting quarterly to revise and update mHealth content and engage in an Appreciative Inquiry Process to evaluate the implementation of the multicomponent health program and determine when refinements for optimization are needed. The co-creation and optimization of the program components will be guided by the contextual domains of PRISM (i.e., intervention characteristics, recipient characteristics, implementation and sustainability infrastructure, external environment) and will build on the team’s prior work with the community [24, 31] and the CAB members’ lived experience as members of their respective communities.

#### mHealth development and outreach

mHealth-related communications will include personalized short messaging service (SMS) and automated phone calls recorded by community leaders in their respective languages aligned with the language preferences of our target clinics. The content of mHealth outreach will include information such as how and where to get vaccinated, myths about COVID-19 and other vaccines, the importance, timing, and scheduling of priority preventive services, and provide reminders for clinical care appointments. The study team includes an expert consultant in health communications to guide message development. mHealth distribution frequency will be determined by each CAB to align with their community’s preferences and needs. New messages will be developed and added to the message library based on updated public health guidance and feedback from participants. The mHealth outreach system will be user tested and refined prior to launch. See Fig. 3 for a schematic of the mHealth outreach system.

**Fig. 3 Fig3:**
[figure not shown]
Schematic of the mHealth outreach system

A mHealth specialist will lead the development of the mHealth delivery system by consulting with programming experts through Twilio to design and build a fully integrated, Health Insurance Portability and Accountability Act (HIPAA) compliant communications platform to manage the distribution of SMS and voice communications. Twilio will allow customized communications, develop production-ready applications, and run serverless applications on one application programming interface-powered platform. A centralized study database connected with the mHealth delivery system will track the number and timing of text and voice messages sent to individual participants. User analytics will be captured such as individual reach, responsiveness, and engagement. Example messages may include the following: “Proteja a sus seres queridos con vacunarse contra el COVID-19”/ “Protect your loved ones by getting the COVID-19 vaccine” and “Recuerde pedir su vacuna contra la Influenza”/ “Remember to ask for your flu shot.”

#### Care coordination

The partnering FQHC has an established process to provide care coordination (see standard of care in Table 2). The partnering FQHC will identify study-specific care coordinators who are members of the three study communities. Care coordination for the intervention will be tailored to the needs and cultural preferences of the respective patient community through input from our CABs. The content of care coordination will include engagement of patients in preventive services, developing a patient health action plan, support with adhering to the health action plan, scheduling preventive and care management appointments, communicating with the patient’s care team to ensure continuity of care, and COVID-19 vaccination.

**Table 2 Tab2:** Summary of the Sequential, Multiple Assignment, Randomized Trial (SMART) design

Standard of Care	Multi-component health program
Aligned with patient-centered medical home components and quality-of-care measures	**Community Weaver led Co-Creation** Overarching strategy
**Care coordination**	**mHealth Outreach**
• Routine immunization efforts • Annual physical exam • Eligibility: defined medical conditions (e.g., uncontrolled diabetes, hypertension), high health services utilization (e.g., > 5 medications), social determinants of health and referred by care team	Community outreach led by Community Weavers via SMS and voice messages about COVID-19 vaccines (importance, reminders, how to access) and preventive services engagement (importance, reminders, how to access) in languages spoken by patients (i.e., Spanish, Arabic, Vietnamese)
	**Care Coordination**
	Inclusive of standard of care coordination with added focus on completing outstanding preventive services (e.g., HbA1c, blood pressure screenings, mammograms, colorectal cancer screening)

### Measures

Data will be collected using multiple sources to represent diverse perspectives using a QUANT + QUAL concurrent mixed-method design approach. Data sources, type, source, and timing of collection as well as key implementation and effectiveness outcomes are summarized in Tables 3 and 4. Surveys and interviews with participants will be conducted in the participant’s preferred language. Participant surveys will be drafted with input from the CABs, pilot tested prior to implementation, and use electronic or paper formats based on participant preferences. Interviews will be led by Community Weavers using a semi-structured interview guide reflecting PRISM domains adapted from prior studies [58, 72] and vetted by the CABs. Interviews will be recorded and translated to English. Study data for mHealth message delivery, care coordination, and Community Weavers will be stored in Research Electronic Data Capture (REDCap). Periodic reflections will be collected as weekly diary entries from members of the research team. Partner engagement will be evaluated using a concurrent mixed-methods approach developed through the team’s NIH-funded COVID-19 projects [68]. A partner engagement survey (Goodman et al.) will be distributed following each CAB meeting to assess how well and how often eight engagement principles were perceived during the meeting [69]. Ethnographic documentation of the CAB process will be conducted by trained research staff using a structured documentation form identifying various aspects of engagement (e.g., topics covered, time spent contributing) [25].

**Table 3 Tab3:** Main data sources, data types, origin, and the domains of the practical, robust implementation and sustainability model (PRISM)

Data source name	Type	Origin	PRISM domains
mHealth message delivery study database (QUANT + QUAL)	#, timing, type, content of message delivery for each language groups	mHealth specialist	Implementation Maintenance
Care coordination study database (QUANT + QUAL)	#, timing, type of care coordination activities	Care coordinators	Implementation Maintenance
Community Weaver study database (QUANT + QUAL)	#, timing, type of interactions with communities	Community Weavers	Implementation Maintenance
Periodic reflections (QUAL)	Key lessons learned, facilitators, challenges of implementation of and adaptations to program components	mHealth specialist Community Weavers Care coordinators Research team	Intervention characteristics Implementation & sustainability infrastructure External environment
Participant user engagement check-in (QUANT)	Acceptability, appropriateness, utility, and value of text/voice messages and care coordination	All participants in mHealth or mHealth & care coordination arm	Reach Implementation Intervention characteristics
Participant evaluation surveys (QUANT)	Satisfaction, engagement, and impact of the multicomponent health program	All participants in mHealth or mHealth and care coordination arm	Implementation Effectiveness Maintenance
Participant interview (QUANT + QUAL)	Acceptability, appropriateness, utility, and value of text/voice messages and care coordination	Subset of participants (*n* = 60, 20 from each clinic)	Implementation Effectiveness Maintenance
Participant vaccine and preventive service status & health characteristics (QUANT)	EHR data on study primary and secondary outcomes, patient demographic, other health characteristics	Care coordinators	Reach Recipient characteristics
Delivery agent survey (QUANT)	Demographic and professional characteristics of Community Weavers and care coordinators	Community Weavers Care coordinators	Recipient characteristics Adoption

*QUANT*, quantitative; *QUAL*, qualitative

**Table 4 Tab4:** Outcome measures summarizing the implementation and clinical effectiveness outcomes

Implementation outcomes	Reach	The absolute number, proportion, and representativeness of participants who are compared to all eligible patients on key characteristics. Reasons for nonparticipation
	Adoption	Demographic and professional characteristics of Community Weavers and care coordinators
	Implementation	#, timing, type, content of delivery of mHealth messages, care coordination, and Community Weaver activities
	Maintenance	Ongoing delivery of mHealth messages, care coordination, and Community Weaver activities during the sustainment phase. Ongoing impact on vaccine acceptance and confidence, COVID-19 vaccine uptake, and preventive services engagement
Effectiveness (clinical) outcomes	Vaccine confidence	Adapted vaccine confidence survey
	Intention to engage in preventive services	Measured as scheduled appointments for due or overdue preventive services
	COVID-19 vaccine uptake	Up-to-date vaccine record defined as completed vaccine series and required boosters as recommended by Centers for Disease Control guidelines for COVID-19 vaccination at the time of implementation to be confirmed through electronic health records
	Preventive services engagement	Up-to-date age- and gender-specific preventive services (e.g., mammograms, adult immunizations, blood pressure screenings, A1c screenings, colorectal cancer screenings). Standards will be defined for each participant based on their demographic and health characteristics

### Power calculations

Primary effectiveness outcomes will be COVID-19 vaccine (initial and bivalent booster) completion at a sustained rate of 70% (consistent with Healthy People 2020 influenza vaccination goal for adults aged 18 + years) [70]. Secondary effectiveness outcomes will be an increase in preventive service engagement defined as completing a physical exam and at least one recommended preventive care screening (e.g., mammogram, A1c screening, colorectal cancer screening) annually and increases in vaccine confidence. Data on other recommended adult immunizations (e.g., influenza, shingles) will be extracted from patient electronic health records (EHRs). Primary implementation outcomes will be reach, adoption, implementation, and maintenance up to 2-year post-implementation. Target sample size was determined using methods described by Kidwell et al. [71] for a SMART design with a binary outcome. A power analysis was conducted to inform our targeted sample size based on the following assumptions: (1) probability of success for adaptive health interventions of 0.70; (2) estimated response rate for standard of care of 0.45 (current vaccination rate among target population); and (3) equal re-randomization after first-stage intervention for nonresponders. Allowing for a 5% type-1 error and 80% power, a sample size of at least 252 is needed to evaluate an effect size of 0.25. Assuming a 15% loss to follow-up during the 2-year intervention period, our target enrollment of 300 participants will ensure sufficient sample size for analysis.

### Analytic approach

Quantitative data from surveys, study databases, and EHRs will be summarized using simple descriptive statistics along with data visualization methods to understand patterns and characteristics of responders and nonresponders and to guide adaptive implementation. Parametric and nonparametric tests will be employed to compare the survey responses between the arms of the trial variables and clinic locations. Factors will initially be assessed at the univariate level and then used to build multivariable models to assess independent associations of multiple factors on vaccination uptake, including community level factors such as prevalence of COVID-19 vaccination, history of COVID-19 infection, and primary community language group. Multinomial logistic regression models will explore the relation between standard of care, mHealth outreach, and mHealth plus care coordination and COVID-19 vaccine uptake, while controlling for a variety of demographic and socioeconomic variables and comorbidities, as well as FQHC clinic characteristics. Additionally, the association between adaptive interventions and the secondary clinical composite outcome, preventive services engagement, including age and gender-specific services will be evaluated. Descriptive analysis will be used to characterize within subgroup differences. Mixed-effects logistic regression models will be used to identify factors associated with COVID-19 vaccine uptake and vaccine confidence using EHR and demographic data collected with participant evaluation surveys.

Qualitative data will be culled from interviews, periodic reflections, and study databases. All qualitative data will be coded using a rapid qualitative data analytic approach guided by the domains of PRISM, informed by prior work of the lead and senior authors across diverse contexts [58, 72, 73]. This approach involves developing a templated matrix of summary responses from interviews, followed by coding by a qualitative analytic team based on pre-defined themes while allowing for new sub-themes to emerge [74]. Group coding for consensus building, team-based review of codes, and double coding to verify acceptable inter-rater reliability will occur throughout the coding process. Community Weavers and clinic partners will be invited to review the coded data to support sense-making and develop action items based on the data.

A matrix approach will be used to triangulate data from quantitative and qualitative sources using the key domains of PRISM. A joint display analysis will be produced to support the integration of data sources [75, 76]. Unique and common themes across language groups will be identified and described.

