**Methods:**

This is a hybrid type 3 effectiveness-implementation study that will include a multi-level, longitudinal, mixed-methods data collection approach designed to assess the sustained impact of a co-created multicomponent strategy relying on bidirectional learning, shared decision-making, and expertise by all team members. The study capitalizes on a combination of implementation strategies including mHealth outreach with culturally appropriate messaging, care coordination to increase engagement in high priority preventive services, and the co-design of these strategies using community advisory boards led by Community Weavers. Community Weavers are individuals with lived experience as members of an underserved community serving as cultural brokers between communities, public health systems, and researchers to co-create community-driven, culturally sensitive public health solutions. The study will use an adaptive implementation approach operationalized in a sequential multiple assignment randomized trial design of 300 participants from three sites in a Federally Qualified Health Center in Southern California. This design will allow examining the impact of various implementation strategy components and deliver more intensive support to those who benefit from it most. The primary effectiveness outcomes are COVID-19 vaccine completion, engagement in preventive services, and vaccine confidence. The primary implementation outcomes are reach, adoption, implementation, and maintenance of the multicomponent strategy over a 12-month follow-up period. Mixed-effects logistic regression models will be used to examine program impacts and will be triangulated with qualitative data from participants and implementers.

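### Vaccine uptake is defined and sized as binary for adaptive interventions, but the Analytic approach gives it a multinomial model and the abstract a mixed-effects logistic model

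*Protocol article*

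**What the plan says.** Four places in the Protocol article bear on how the vaccine endpoint is analysed.

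- **Measures, Table 4.** Uptake is an "Up-to-date vaccine record defined as completed vaccine series and required boosters" under the guidelines then in force. A participant is up to date or is not.
- **Power calculations.** The vaccine endpoint is the primary effectiveness outcome, and the sample size uses a method "for a SMART design with a binary outcome". The inputs are a "probability of success for adaptive health interventions of 0.70" and an "estimated response rate for standard of care of 0.45 (current vaccination rate among target population"), with equal re-randomization of nonresponders, 5% type-1 error and 80% power. The result is at least 252 participants, with 300 enrolled to allow for 15% loss.
- **Analytic approach.** The comparison of strategies is stated as "Multinomial logistic regression models will explore the relation between standard of care, mHealth outreach, and mHealth plus care coordination and COVID-19 vaccine uptake", with covariate adjustment. Later in the same paragraph, "Mixed-effects logistic regression models will be used to identify factors associated with COVID-19 vaccine uptake and vaccine confidence".
- **Abstract, Methods.** "Mixed-effects logistic regression models will be used to examine program impacts".

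**The concern.** The endpoint has two levels, but the model named for comparing strategies is one for three or more unordered outcome categories. Read literally, either uptake has a third category that the article never defines, or the strategy group is the dependent variable and the roles of treatment and outcome are reversed. The abstract names a different model for program impacts, and the Methods give that model another job.

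The groups compared do not match either. The power section concerns adaptive interventions. The multinomial sentence lists three strategies and leaves out standard of care followed by care coordination, which the Design section creates by re-randomizing standard-of-care nonresponders.

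This is the endpoint on which the trial is sized. A marginal logistic model and a mixed-effects logistic model give odds ratios that are not interchangeable, and neither named model is marked as primary. A choice made after the results are seen could change the headline effect.

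**Working it through.** **1. Reproduce the stated sample size.** Inputs from Power calculations: p1 = 0.70, p2 = 0.45, 5% type-1 error (two-sided assumed), 80% power, equal re-randomization. For two embedded adaptive interventions that start with different first-stage treatments, on the log odds ratio scale with first-stage response rate r:

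N = 2(2 − r)(z₀.₉₇₅ + z₀.₈₀)² [1/(p1q1) + 1/(p2q2)] / (log OR)²

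- OR = (0.70/0.30)/(0.45/0.55) = 2.852; log OR = 1.048
- 1/0.21 + 1/0.2475 = 8.802
- (1.960 + 0.842)² = 7.849
- With the conservative r = 0: N = 4 × 7.849 × 8.802 / 1.048² = 251.6, rounded up to 252
- Loss to follow-up: 252/0.85 = 296.5, so 297, within 300

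The same calculation on the risk-difference scale gives 4 × 7.849 × (0.21 + 0.2475)/0.25² = 229.8, so 230. The stated 252 therefore fits a binary outcome, a marginal odds ratio of 2.85, and a contrast between adaptive interventions.

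**2. Multinomial model on the documented endpoint.** With two outcome levels, multinomial logistic regression is ordinary logistic regression. A fit of both to the same simulated binary data gave identical coefficients (−0.255, 1.172) and standard errors (0.180, 0.267). Estimate, test and power do not change.

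**3. Mixed-effects logistic model.** The article does not say what the random effect is. For a normal random intercept with SD s, solve numerically for the conditional log odds b at which the average of 1/(1 + exp(−(b + u))) over u ~ N(0, s²) equals 0.45, and again for 0.70. The conditional odds ratio is the exponential of the difference between the two solutions. The intraclass correlation is s²/(s² + π²/3).

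| Random intercept (assumed) | SD | Intraclass correlation | Conditional OR for 0.45 vs 0.70 |
|---|---|---|---|
| none (marginal) | 0 | 0 | 2.85 |
| clinic | 0.18 | 0.01 | 2.88 |
| clinic | 0.42 | 0.05 | 2.97 |
| clinic | 0.60 | 0.10 | 3.11 |
| clinic | 0.91 | 0.20 | 3.41 |
| person, repeated status | 1 | 0.23 | 3.53 |
| person, repeated status | 2 | 0.55 | 5.56 |
| person, repeated status | 3 | 0.73 | 9.58 |

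Every row describes the same two population proportions. Estimate and standard error scale up together, so power should change little; what changes is the number reported.

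**4. Groups compared.** If the three strategies in the multinomial sentence mean treatment received, take 252/2 = 126 per first-stage arm and, for illustration, apply the 0.45 response rate to both arms. Then 126 × 0.55 / 2 ≈ 35 people receive mHealth plus care coordination. Those still on standard of care would all be responders, since every nonresponder there is moved to something else. The 252 calculation does not cover that comparison.

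**The case against.** The strongest reply is that little of numerical consequence follows from the text as written.

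- **Power.** A reader might infer that the multinomial model loses power. A 2-df test at the planned noncentrality of 7.85 has 71% power against 80% on 1 df. With an assumed partial category of 10%, 20% or 30% in controls, power for up to date versus none at 252 would be 75%, 68% or 57%. The article does not support this reading: it defines no partial category, and step 2 shows no loss on the endpoint it does define. This objection stands in full.
- **Odds ratio.** A reader might also infer that the mixed model inflates the effect several-fold. That needs repeated vaccine status, a person-level intercept and a large SD, none of which the article states. The longitudinal design makes a person effect plausible. With three recruiting clinics, a clinic intercept is as open a reading, and then the shift is small. A conditional odds ratio is also a different estimand, not a wrong one. This too stands.
- **Article format.** The abstract's phrase on program impacts follows a list of several outcomes and is not tied to vaccine uptake alone. The multinomial models are said only to explore. Details such as random-effects structure and time point are commonly left to a full protocol or SAP, and their absence is no finding. This softens the conflict but does not remove it: the Methods still name a model that does not fit the endpoint, and the abstract gives mixed-effects models a role that the Methods do not.

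**Conclusion.** The point holds as an inconsistency in the stated analysis of the endpoint on which the trial is sized. Table 4 and the power section agree on a binary outcome, and 252 reproduces on a marginal odds ratio of 2.85 for adaptive interventions, assuming a two-sided test and r = 0. The multinomial model does not match that endpoint, its three listed groups are not those adaptive interventions, and the abstract and Methods give the mixed-effects model different roles.

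On the documented endpoint the multinomial term is a mislabel without power loss. Following the abstract would move the reported odds ratio from 2.85 to about 2.9 to 3.4 under a clinic intercept, or 3.5 to 9.6 under a person intercept. Both ranges rest on assumed variances. Neither reduced power nor a several-fold inflation can be claimed from the document. The correction is still worth making: it is cheap and removes a choice of model that could otherwise be made after the data are seen.

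**What to change.** In the Analytic approach, replace the multinomial model with one primary binary logistic model for up-to-date vaccine status at a fixed time. It should estimate the marginal contrast between the embedded adaptive interventions that the power section covers. Because only nonresponders are re-randomized, the model needs weights: with equal allocation at both stages, responders are randomized once (weight 2) and re-randomized nonresponders twice (weight 4). Use a robust variance. An unweighted population-average model would not estimate these contrasts.

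Report the odds ratio, the scale on which 252 reproduces, and alongside it the difference in proportions with a 95% CI. Keep mixed-effects logistic regression for the associated-factors analyses, and make the abstract's sentence on program impacts agree.

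The cost is wording in two places and standard software. No new data are needed and 252 stands. The reported odds ratio may be smaller than a conditional one would have been.
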